### Outcome measures: Assessment, blinding, and rationale

The PUSH assessed objective and subjective outcomes of physical performance in addition to hemodynamic, cardiorespiratory, and cardiometabolic risk variables. Outcome assessments were done upon admission (baseline), facultatively at week 2 and at week 4 (Table 1). All participants, direct care providers and assessors were masked to the outcomes under investigation throughout the study. Whereas, participant and care providers were blinded by categorically withholding supplementary information on the glycemic control categories described above and exposures under investigation, main outcome assessors (therapists and laboratory technicians) were masked by complete prohibition of access to patient medication data as per previously established institutional policy.

**Table 1 T1:** Assessment time plan.

**Assessment**	**Time points during study**		
	**Baseline** ^a^	**Week 2**	**Week 4**
Screening for inclusion and exclusion criteria	°		
Participant characteristics^b^	°		
Status of medications^c^	°	°	°
Anthropometric and clinical parameters^d^	°	°	°
Laboratory tests^e^	°	°	°
Rehabilitation outcomes^f^	°	°	°
Transthoracic echocardiography^g^	°		°
Sonographic assessment of liver parenchyma (NAFLD)^h^	°		°
Muscle sonography^i^	°	°	°
Monitoring for adverse events^j^	Throughout stay		

a *Baseline was defined as the date of eligibility confirmation and inclusion in the study. If no data were available at baseline, the most recent data from the hospitalization prior to admission were used*.

b
*Included information on age, sex, medical history, complications and comorbidities, smoker status, coffee consumption.*

c
*Included antidiabetic agents, antihypertensives, lipid-lowering drugs, thrombocyte aggregation inhibitors, therapeutic anticoagulation, use of proton pump inhibitors, uric acid lowering drugs, antidepressants, opiates, NSAIDs, neuropathic pain treatment, vitamin D, iron, calcium, and magnesium substitution.*

d
*Included body weight, BMI, waist and hip circumferences, estimation of skeletal muscle mass in kg using the Baumgartner equation, mean systolic and diastolic blood pressures, mean fasting plasma glucose (for all groups at baseline, for group I and II at week 2 and 4), peak expiratory flow rate, state of nocturia, pain numeric rating scale [NRS] (range 1–10).*

e

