### Sample size and data analysis

#### Sample size

Based on the results of the cardiovascular heart study of Enright et al., among 2,281 community dwelling adults ≥68 years old, the expected mean 6-min walk distance (6MWD) was 344 ± 88 m which is the set target of exercise therapy in rehabilitation (45). Centered on our clinical observations and on the results of a small pilot study in the clinical rehabilitation of patients with cerebrovascular disease (121), we assumed a mean 6-MWD at baseline of 250 m with an anticipated improvement of 80 ± 40 m after 4 weeks of exercise therapy. To detect an additional difference of ±15%, as reported in previous studies on this subject (28), within the group as well as between any 2 groups with power of 80 % and an alpha error of 5% using a 2-sided test after 4 weeks, the sample size required was 130 participants per group. Based on our admission statistics, the attrition rate for administrative reasons, mainly being lack of insurance coverage for a treatment duration of at least 20 days, was estimated at 15 %, while 85 % of participants were expected to complete the week 4 follow-up. To this end, 150 participants per group needed to be enrolled (450 participants in total).

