#### Data analyses

Demographic data will be examined using independent-samples *t*-tests and Fisher's exact tests for dichotomous variables. Independent-samples *t*-tests and repeated-measures ANOVAs will be employed to compare changes in physical performance after 4 weeks. Differences between primary and secondary outcome variables after 4 weeks will also analyzed by linear mixed-effects models (LMMs). The time factor for the model will be set at baseline and week 4. The models will include model-based adjustments for baseline characteristics influencing physical performance in such cohorts: (1) age, sex, BMI, waist circumference, diabetes duration and history of cardiovascular disease.

To minimize the bias that could result from participants in the 3 groups having highly variable duration of stay, the prospective analyses will be performed on a modified intention-to-treat and per protocol basis. The modified intention-to-treat population will be defined as participants who have been categorized to a study group and have at least one follow-up measurement of the primary outcomes, regardless of treatment adherence or duration of stay. The “last observation carry-forward method” will be used in the absence of complete follow-up data. For “per protocol” analysis, only those participants who have follow-up measurements after a minimum treatment duration or length of stay of ≥20 days will be included.

Sensitivity analyses will be performed to account for potentially non-ignorable missing data due to dropout as well as the possible impact of other potentially influential variables. A Bonferroni correction will be applied to the LMM analyses of the primary and secondary outcomes.

Pre-specified subgroup analyses will be conducted; these will include subgroups defined according to the various entities of ASCVD, gender, age groups, and other factors.

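### LOCF in a baseline/week-4 model counts early walk distances as week-4 values; this dilutes group differences, and biases them if early leaving differs between groups

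*Protocol article*

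**What the plan says.** All references are to the Protocol article.

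- **Missing follow-up (Data analyses):** "The “last observation carry-forward method” will be used in the absence of complete follow-up data".
- **Analysis set (Data analyses):** the mITT set needs one follow-up value of the primary outcomes and sets no condition on adherence or stay. LOCF therefore carries forward a post-baseline value, not the baseline itself.
- **Model (Data analyses):** "The time factor for the model will be set at baseline and week 4".
- **Visits (Outcome measures):** "Outcome assessments were done upon admission (baseline), facultatively at week 2 and at week 4". Table 1 lists the 6-minute walk test at all three times.
- **Expected course (Sample size):** "we assumed a mean 6-MWD at baseline of 250 m", "with an anticipated improvement of 80 ± 40 m after 4 weeks of exercise therapy". Attrition is put at 15% overall, mainly because insurance does not cover at least 20 days. No figure is given by group.
- **Stated purpose (Data analyses):** the two analysis sets are meant to limit bias from widely varying length of stay in the three groups.
- **Other safeguards (Data analyses):** a per-protocol set, in which "only those participants who have follow-up measurements after a minimum treatment duration or length of stay of ≥20 days will be included", and sensitivity analyses for dropout that may be informative, with no method named.
- **Missing baseline (Table 1, footnote a):** "If no data were available at baseline, the most recent data from the hospitalization prior to admission were used".

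**The concern.** LOCF assumes that a participant stops changing after the last test. The plan's own sample-size assumption is that walk distance keeps rising during rehabilitation. Because the model has only two time levels, a value from week 2 or an early discharge can enter only by being labelled week 4. A shorter stay then looks like a smaller response.

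The groups are formed by glycaemic status and treatment, not by randomisation, so nothing in the design balances length of stay between them. If one group tends to leave earlier, part of that difference is reported as a difference in physical performance. That is the bias the section says it wants to limit, and it falls on the primary outcomes.

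**Working it through.** **Inputs from the Sample size section.** Baseline 250 m; gain 80 m with SD 40 m over 4 weeks; effect of 15%; 80% power, two-sided 5%; 130 per group, 150 enrolled; 15% without week-4 follow-up.

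**The target difference.** The text says "To detect an additional difference of ±15" per cent but does not state the base. Using n per group = 2 × (1.96 + 0.84)² × SD² / difference², with SD 40 m:

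| Base | Difference | n per group |
|---|---|---|
| 80 m gain | 12 m | 175 |
| 344 − 250 = 94 m | 14.1 m | 127 |
| 250 m baseline | 37.5 m | 18 |

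The stated 130 is not reproduced from 12 m; only the 94 m base, which the text does not name, comes close. I use 12 m below because it is the plain reading of an additional difference in an 80 m gain, but it remains an assumption. The sample size itself is a separate matter.

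**Shortfall of a carried value (linear gain assumed).** 80 / 28 = 2.86 m per day. A day-14 value is 14 × 2.86 = 40 m short of week 4. A day-20 value is 8 × 2.86 = 22.9 m short.

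**False group difference with no true effect.** Bias = (difference in early-leaver shares) × (shortfall). The shares are scenarios, each averaging the planned 15%. The standard error with 150 per group is 40 × √(2/150) = 4.62 m.

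| Early leavers | Day-14 value | Type I error (nominal 5%) |
|---|---|---|
| 15% vs 15% | 0 m | 5% |
| 10% vs 20% | 0.10 × 40 = 4 m | 14% |
| 5% vs 25% | 0.20 × 40 = 8 m | about 40% |

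A simulation (4,000 runs, 150 per group, SD 40 m) gave LOCF differences of 0, 4.1 and 8.1 m in size. A likelihood analysis keeping week 2 as its own time point gave 0.1 m or less, with type I error of 5–6%. The simulation had a week-2 value for everyone, which an optional visit will not guarantee.

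**If the gain is front-loaded (assumed).** With 65% of the gain reached by week 2 the shortfall is 0.35 × 80 = 28 m; with 80% it is 16 m. The 10% vs 20% case then gives 2.8 m or 1.6 m, and the 5% vs 25% case 5.6 m or 3.2 m.

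**Effect on a true 12 m difference (gains 80 and 92 m, linear, day-14 values).**
- Equal 15% shares: 0.85 × 12 + 0.15 × 6 = 11.1 m.
- Better group 20% early, other 10%: (0.8 × 92 + 0.2 × 46) − (0.9 × 80 + 0.1 × 40) = 82.8 − 76 = 6.8 m.
- Reversed: (0.9 × 92 + 0.1 × 46) − (0.8 × 80 + 0.2 × 40) = 87.4 − 72 = 15.4 m.

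The error can therefore go either way. The dilution under equal shares requires that the group difference itself grows between week 2 and week 4.

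**The case against.** **Stay by group is unknown.** The protocol gives one overall attrition figure, mainly administrative, and says that stay varies, not that its mean differs between groups. With equal early leaving LOCF creates no false difference. This stands. A reader might infer that the plan will produce a false finding; the documents support only that the rule permits one, of unknown sign and size.

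**Linearity and the 12 m target are assumptions.** This also stands. Against 37.5 m, a 4 m bias would be 11% rather than a third. The ranges above reflect the first point, and the second cannot be settled from the text.

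**The plan has other safeguards.** They help only in part. The per-protocol set removes the shortest stays, but it selects on something that happens after baseline. It sets a 20-day minimum without an upper window, so two patients in it may be tested at points where expected distance differs by up to 22.9 m. That is a spread between individuals, not a group difference. The sensitivity analyses may be well specified elsewhere, but LOCF remains the stated mITT rule.

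**Stronger readings that the documents do not support.**
- Footnote a might be taken to distort the primary outcome by a calculable amount. A baseline 6-minute walk is needed to apply the exclusion below 25 m, so substitution may rarely touch that outcome, and the rehabilitation slope cannot be applied to days before rehabilitation.
- The per-protocol wording might be read as admitting Group I patients who stopped the drug early. The phrase is ambiguous and does not establish this.
- LOCF might be said to understate standard errors here. No calculation shows it, and the type I error was 5% with equal shares.

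**Conclusion.** The point holds as a defect in the stated mITT rule. LOCF combined with a two-level time factor treats early values as week-4 values of an outcome the plan expects to rise. It dilutes a difference that builds up over time (12 m to about 11.1 m with 15% early leavers in each group), and it biases the comparison if early leaving or day of last test differs between the groups.

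Under linear gain and day-14 last values, the false difference is one third of a 12 m target at 10% vs 20% early leavers and two thirds at 5% vs 25%. It is smaller if the gain is front-loaded and nil if the shares are equal. These are scenarios, not estimates for this study. The same rule governs the other primary outcomes, for which the documents give no expected change from which to size the bias.

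**What to change.** 1. Make the main mITT analysis a linear mixed model on all observed baseline, week-2 and week-4 values, without LOCF. Give week 2 its own time level, or use the actual day of assessment where recorded, and estimate group differences at week 4.
2. Keep LOCF and the 20-day set as sensitivity analyses.
3. Report length of stay and day of last 6-minute walk test by group, so that readers can judge whether the concern materialised.
4. Secondary point: for outcomes analysed as change, do not fill a missing baseline with a pre-admission hospital value. The effect cannot be sized from the documents and probably concerns secondary outcomes more than walk distance.

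**Cost.** The analyses are described in the future tense, so this is a change of analysis wording using data from scheduled visits; it should be fixed before groups are compared. Intervals will be slightly wider. The model relies on missing-at-random, which is plausible where insurance cover ends a stay but not guaranteed, and on optional week-2 data that may be sparse. The protocol does not confirm that every assessment date was recorded, which is why week 2 as a time level is the default.

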## Discussion

The PUSH is a a real-world, 4-week prospective, three-arm observational study designed to evaluate the impact of glycemic control and guideline-directed medical therapy with an SGLT2i on physical performance of patients with established ASCVD or high cardiovascular risk.

Prior research suggests that there is a strong correlation between physical performance and the risks of cardiovascular disease and mortality (62, 122). It is also clear that treatment with SGLT2is reduces the risks of heart failure hospitalisations, progression of renal disease, cardiovascular disease and mortality in individuals with T2D with changes seen early within a few weeks after the begin of treatment (20–22). Therefore, unlike previous pilot studies on the subject (27–31), the PUSH incorporated strategies to investigate change in physical performance in a larger cohort of individuals with established ASCVD or high cardiovascular risk under guideline-directed medical therapy. Because change in physical performance is highly dependent on both oxygen delivery and utilization systems (123), the PUSH assesses cardiac, respiratory and muscle parameters related to physical performance. Thus, much effort was made in the design to have an extensive assessment of variables impacting exercise capacity as previously described in similar cohorts (1). In analyzing or adjusting for these variables, the results of the PUSH could be of clinical relevance in the management of patients with T2D and established ASCVD or high cardiovascular risk.

Due to demographic factors, the clinical and economic costs related to ASCVD are expected to increase dramatically in coming years. Consequently, the identification of therapy regimes capable of reducing ASCVD disease burden is an important goal with remarkable public health repercussions (124).

The PUSH design however has some limitations. First, the non-randomized design precludes analyses and conclusions of the causal relationships among variables. Second, despite efforts to address the internal validity threats, the selection bias of using glycemic control to determine participants for the guideline-directed medical therapy with an SGLT2i remains an important threat in the interpretation of the results even though a previous study in this field did not show any negative impact of suboptimal glycemic control under treatment with an SGLT2i (dapagliflozin 10 mg) on the physiological adaptation to endurance exercise training (31). Accordingly, studies on changes in physical performance under SGLT2is in patients with both inadequately and adequately controlled T2D are still warranted. Third, the prospective design of this study with a follow-up of just 4 weeks addresses solely the hypothesis of early changes in physical performance under guideline-directed medical therapy with an SGLT2i. Further studies will be necessary to investigate, if present, the extent and sustainability of these early changes over a longer period of observation with or without endurance exercise therapy. Finally, we will not compare participants to those who did not receive inpatient rehabilitation after a medical or surgical condition warranting inpatient rehabilitation, as such, the potentiating effect of exercise therapy during rehabilitation on the results shall not be easily quantified.

## Study status

The first participant was recruited in January 2018. Data collection was concluded in September 2020 when the target of 450 participants was met. The SARS-COVID global pandemic delayed patient enrollment and data collection between February and September 2020 but neither relevantly influenced the study protocol nor the rehabilitation program. The publication of the results is expected in 2022.

## Ethics Statement

Written informed consent was obtained from the individual(s) for the publication of any potentially identifiable images or data included in this article.

